### Ethical Considerations

This study was approved by the Noninterventional Clinical Research Ethics Committee of Istanbul Medipol University (E-10840098‐202.3.02-4331, July 18, 2024). The research will be conducted in accordance with the principles of the Declaration of Helsinki. Written and verbal information will be provided to the parents of children who meet the inclusion criteria. Parents of children who agree to participate will be asked to sign an informed consent form. Children will also receive age- and developmentally appropriate information about the study procedures, and those who are unwilling to participate will not be included in the study. The informed consent form states that participation in the study is voluntary and free of charge. Participants will retain the right to withdraw from the study at any time. No additional fees will be collected from the participants, nor will any payments be made. The personal data and identity information of the participants will be kept confidential. Electronic data will be stored in password-protected files, and paper-based documents will be kept in locked cabinets accessible only to the research team. No biological specimens will be collected in this study. The data will be used solely for scientific purposes, without any commercial intent. As the intervention is considered low risk, a data monitoring committee was not established. Participant safety and data integrity will be monitored by the principal investigator.

### Study Design

This study is registered at ClinicalTrials.gov (NCT07311018) and is designed as a 2-arm, parallel-group, randomized controlled trial (RCT) with a 1:1 allocation ratio. The study is planned to be conducted in the laboratory of the Physiotherapy and Rehabilitation Department at Istanbul Medipol University. The necessary institutional approvals have been obtained. A demographic information form will be completed for the participating children and/or their parents to collect data on age, birth history, sex, diagnosis, surgical history, medication use, family history, limb involvement, dominant side, use of assistive devices (eg, hand splint, orthosis), and whether the child is enrolled in a hand rehabilitation program at the time of this writing. The flow chart of the study is shown in Figure 1.

**Figure 1. F1:**
[figure not shown]
Study flow diagram. EMG: electromyography; NMES: neuromuscular electrical stimulation.

### Randomization and Allocation

Patients who meet the inclusion criteria and agree to participate will be randomly assigned to one of 2 groups using a computer-based randomization program [28]. Block randomization will be applied to ensure balanced group sizes, with 15 participants allocated to each group (n=15). The random allocation sequence will be generated by an independent researcher who is not involved in participant enrollment, assessment, or intervention delivery. Allocation concealment will be ensured using sequentially numbered, opaque, sealed envelopes prepared prior to the 8-week intervention. Investigators responsible for participant recruitment and outcome assessment will not have access to the randomization sequence. Due to the nature of the interventions, blinding of participants and the treating physiotherapist will not be feasible. However, outcome assessments and statistical analyses will be conducted by assessors who are blinded to group allocation.

### Eligibility Assessments

To assess eligibility according to the inclusion criteria, the following evaluations will first be performed in participating children: gross motor function will be assessed using the GMFCS, manual ability level will be evaluated using the MACS, and upper extremity muscle spasticity will be measured using the MAS.

#### GMFCS

The GMFCS is based on the self-initiated movements of children with CP, emphasizing sitting, transfers, and mobility. This classification system consists of 5 levels. The distinctions between levels are determined primarily by functional limitations, the need for assistive mobility devices (such as walkers, crutches, wheelchairs, or canes), and, to a lesser extent, by the quality of movement. During the assessment, gross motor skills are evaluated considering both the child’s abilities and the limitations in motor function. Children at Level 1 walk without restrictions, those at Level 2 walk with limitations, children at Level 3 walk using handheld mobility devices, those at Level 4 have limited self-mobility and may use powered mobility, and children at Level 5 are transported in a manual wheelchair. Considering the age-related differences in motor function, the GMFCS is categorized for children less than 2 years, 2-4 years, 4‐6 years, 6‐12 years, and 12‐18 years [29].

#### MACS

MACS was developed to classify how children with CP use their hands when handling objects in daily activities, reflecting typical hand performance rather than maximal capacity. The classification describes how children usually use their hands to handle objects at home, at school, and in the community, rather than their best possible performance. It evaluates the ability to handle objects in children with CP aged 4‐18 years. The system consists of 5 levels: children at Level 1 can handle objects easily and successfully, although they may have difficulties with speed and accuracy in activities. Children at Level 5, however, cannot handle objects effectively and have severely limited abilities, requiring support to perform even the simplest hand activities [30].

#### MAS

The severity of spasticity will be evaluated using the MAS**,** which is widely used to quantify resistance perceived during passive movement [31]. The MAS grades muscle tone on a 0‐4 scale. Starting from 0: no increase in muscle tone; 1: slight increase in muscle tone, characterized by a minimal resistance at the end of the ROM; 1+: slight increase in muscle tone, characterized by a catch followed by minimal resistance through less than half of the ROM; 2: more marked increase in muscle tone through most of the ROM, but the affected part is easily moved; 3: considerable increase in muscle tone, making passive movement difficult; and 4: affected part rigid in flexion or extension. In children with CP, spasticity most frequently involves the upper extremity muscles, particularly the shoulder flexors, adductors, and internal rotators; elbow flexors; forearm pronators; wrist flexors; and finger flexors [32,33]. Accordingly, spasticity of these muscle groups in both upper extremities will be assessed using the MAS in this research.

### Outcome Measures

The primary outcome of this study is hand function, and the secondary outcomes are wrist extensor and flexor muscle activation, wrist ROM, wrist selective motor control, and hand use in daily activities. The baseline assessments (T0) will be done after enrollment. Before randomization, all participants will complete a 4-week standardized upper extremity–focused conventional therapy program, which will be conducted as a baseline standardization period to reduce the potential influence of previous routine rehabilitation programs. This phase will not be considered part of the randomized intervention comparison. Postconventional exercise assessments (T1) will be conducted after a 4-week conventional therapy program. Randomization will be performed after the T1 assessment to allow comparison of the additional effects of NMES and Leap Motion–based training when added to the standardized conventional exercise program. The final assessments (T2) will be performed after 8-week NMES and Leap Motion–based interventions. The main comparison will be based on the change from T1 to T2 between the intervention groups. A randomized controlled design was selected to minimize selection bias and to ensure balanced baseline characteristics between the intervention groups. The inclusion of 3 assessment time points (T0, T1, and T2) allows differentiation between the effects of conventional therapy and intervention-specific effects.

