## Methods

### Participants

The sample size was calculated using the G*Power (version 3.1.9.7; Heinrich Heine University Düsseldorf, Düsseldorf) program, with the Jebsen-Taylor Hand Function Test (JTHFT) selected as the primary outcome measure and an assumed effect size of *f*=0.5 selected with reference to a previous study [26]. The calculation was performed with a statistical power of 95% and α=.05, in line with previous research using technology-assisted intervention in CP [27], yielding a minimum required sample size of 24 participants. Considering a 20% attrition rate, a total of 30 participants, with 15 participants in each group, was considered appropriate. The sample size calculation was based only on the primary outcome measure; secondary outcomes were considered exploratory and were not independently used for power estimation.

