### Inclusion Criteria for the Study Are as Follows

Diagnosis of spastic unilateral or bilateral CP confirmed by clinical and magnetic resonance imaging findings, involvement of the distal upper extremity (wrist and/or fingers), being between 6 and 15 years of age, no botulinum toxin injections or surgical interventions applied to the upper extremity within the past 6 months, Gross Motor Function Classification System (GMFCS) levels 1-3, Manual Ability Classification System (MACS) levels 1-3, upper extremity spasticity graded as 0, 1, or 1+ according to the Modified Ashworth Scale (MAS), passive wrist extension angle limitation not exceeding 10 degrees, and ability to follow instructions (mental level documented as “normal” or “mild intellectual disability” in the medical report.

Exclusion criteria were defined as follows: enrollment in a specific hand rehabilitation program at the time of this writing, presence of visual or hearing impairments, history of epilepsy, and presence of chronic, orthopedic, or other systemic conditions that may interfere with participation in the study.

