### NMES Group

For NMES application, a portable 4-channel device (Globus Premium-400; Globus Corporation Srl) will be used. The NMES provides a biphasic waveform, with a pulse duration ranging between 50 and 300 μs and a frequency range of 1‐120 Hz. In spastic CP, stimulation frequencies between 10 and 60 Hz are generally recommended to elicit motor activation, although frequencies above 50 Hz may induce muscle fatigue [43]. In this study, stimulation parameters will be set to a pulse duration of 300 μs, a frequency of 30 Hz, and an on/off ratio of 10 s/10 s [44]. The stimulation intensity will be increased until visible muscle contraction is observed and will then be adjusted to the maximum level tolerated by the participant. The intervention will be administered for 20 minutes per session, in addition to the conventional exercise program, over a period of 8 weeks. Electrode placement will be as follows: the inactive electrode on the dorsal aspect of the wrist, and the active electrode on the lateral forearm over the bellies of wrist extensor muscles (extensor carpi radialis longus and brevis, extensor carpi ulnaris). For participants with bilateral spastic CP, stimulation will be applied to the dominant side, whereas for those with unilateral spastic CP, it will be applied to the affected side. During the first 2 weeks, NMES will be applied passively (Figure 4A). In subsequent sessions, active participation will be encouraged by asking participants to perform wrist extension synchronously with the stimulation (Figures 4B and 4C). During the sessions, children will be monitored for pain, discomfort, muscle fatigue, skin irritation, redness at the electrode site, or any adverse response. Any adverse events will be recorded, and the session will be stopped if necessary.

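### Randomisation is said to ensure balanced baseline characteristics, but the blocks described balance only group size, and the stated primary analysis does not use CP type, which is known before allocation and decides which limb NMES treats

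*Protocol article*

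**What the plan says.** - **Claimed property.** Outcome Measures in the protocol article says the randomised design was chosen to limit selection bias and "to ensure balanced baseline characteristics between the intervention groups".
- **Method.** Randomization and Allocation: "Block randomization will be applied to ensure balanced group sizes, with 15 participants allocated to each group". The section also covers the computer program, the independent sequence generator and the sealed envelopes. It names no stratification factor and no minimisation.
- **Size.** Participants: "a total of 30 participants, with 15 participants in each group, was considered appropriate", from a minimum of 24 plus 20% attrition.
- **Population.** The inclusion criteria admit both types: "Diagnosis of spastic unilateral or bilateral CP confirmed by clinical and magnetic resonance imaging findings". CP type is therefore established at screening.
- **Timing.** Outcome Measures places randomisation after the T1 assessment, so CP type is on file well before an envelope is opened.
- **Role of CP type in treatment.** NMES Group: "For participants with bilateral spastic CP, stimulation will be applied to the dominant side, whereas for those with unilateral spastic CP", the affected side is stimulated.
- **Analysis.** Statistics describes a two-way repeated-measures ANOVA with group, time and their interaction. Outcome Measures makes the T1-to-T2 change the main comparison. No CP-type term is mentioned.

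**The concern.** Blocking forces the numbers per arm to agree and does nothing for the make-up of the arms. With 30 children, a binary feature such as CP type can fall unevenly by chance, so the word *ensure* promises something the described scheme does not deliver.

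CP type is the feature to single out. It may carry prognostic information, and in the NMES arm it also determines which limb is stimulated. If one arm held clearly more unilateral children, a reader of the results could not easily separate the modality effect from the case mix, and the model as stated would not help. The information needed to deal with this is already collected before allocation.

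**Working it through.** **Inputs**
- 30 children, 15 per arm (Participants; Randomization and Allocation).
- Share of unilateral CP: the Introduction gives one-third for spastic CP in general. The trial's expected mix is not stated, so one-third (10 of 30) and one-half (15 of 30) are both used as assumptions.
- Block size: not given, so 2, 4 and 6 are tried.

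**The plan's own figure.** 24 / (1 − 0.20) = 30, or 15 per arm. This agrees with the article.

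**Step 1. Exact calculation for a 15/15 split.** With K unilateral children among 30, the number X falling in one arm has P(X = x) = C(K, x) · C(30 − K, 15 − x) / C(30, 15), where C(30, 15) = 155,117,520. The difference between arms is |2X − K|.

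For K = 10:
- The counts for x = 0, 1, 2, 3 are 15,504; 387,600; 3,488,400; 15,116,400. The upper tail mirrors them.
- 7 v 3 or worse (difference of 4 or more): 2 × 19,007,904 / 155,117,520 = 24.5%.
- 8 v 2 or worse (difference of 6 or more): 2 × 3,891,504 / 155,117,520 = 5.0%.

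For K = 15 only odd differences are possible:
- 9 v 6 or worse (3 or more): 46.6%.
- 10 v 5 or worse (5 or more): 14.3%.

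**Step 2. Permuted blocks, with CP type arriving at random.** Simulation, 30,000 trials per row. It averages over the odd and even counts that make Step 1 jump.

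| Unilateral share | Block size | Difference ≥ 4, unstratified | Difference ≥ 6, unstratified | Largest difference if stratified by CP type |
|---|---|---|---|---|
| 1/3 | 2 | 17.6% | 3.3% | 1 |
| 1/3 | 4 | 17.9% | 3.3% | 2 (in 8.4%) |
| 1/3 | 6 | 17.7% | 3.3% | 3 (in 1.7%) |
| 1/2 | 2 | 19.5% | 4.1% | 1 |
| 1/2 | 4 | 21.0% | 4.8% | 2 (in 8.7%) |
| 1/2 | 6 | 20.6% | 4.3% | 3 (in 1.8%) |

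Block size hardly matters, as expected of a device that controls only group size.

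**Step 3. What an uneven split does to the contrast.** Let D be the difference in mean T1-to-T2 change between unilateral and bilateral children. A 7 v 3 split makes the unilateral shares 7/15 and 3/15. The unadjusted between-arm difference then moves by (7/15 − 3/15) × D = 0.27 D. The article gives no value for D, so the shift cannot be put in seconds.

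**Step 4. Price of adjustment.** Regressing the T1-to-T2 change on group alone leaves 30 − 2 = 28 residual degrees of freedom. Adding CP type leaves 27. With 24 completers the figures are 22 and 21.

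**The case against.** **The sentence is ordinary loose wording.** It explains why the trial was randomised and does not describe the blocks, which the article separately ties to group size. This largely stands. The two sections do not contradict each other, and only the verb is too strong.

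**Strata may exist elsewhere.** This is a condensed article, and a fuller protocol or analysis plan could name strata or covariates. That stands too, so the absence of strata is not by itself an error. The point rests on the assurance the article gives and on the model it does state. A detailed allocation section that gives group size as the purpose of blocking supports reading it as a single list.

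**Chance imbalance is already paid for.** A reader might infer that an uneven split would bias the trial or be reported as a false modality effect. The documents do not support this. Randomisation balances CP type in expectation, and the type I error already allows for chance imbalance.

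**Baseline hand function.** A reader might also worry about a chance gap in T1 Jebsen-Taylor (JTHFT) scores. The main comparison is the change from T1 to T2, which removes much of any stable difference in level, so the probability of such a gap is not the probability of a misleading result.

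**Inputs and link to outcome.** One-third unilateral is a population figure, and the trial selects on distal upper-limb involvement, GMFCS and MACS. Hence the range. Nothing in the article says that JTHFT change differs by CP type. The minimal important differences in the Discussion are by more and less affected hand, so they cannot stand in for D.

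**Re-stratifying mid-trial.** Eleven children were enrolled by June 2026, the strata would be small, and one unblinded physiotherapist delivers both arms. This objection stands, and it is why stratification is only optional here.

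**Conclusion.** The point holds as an overstated assurance and a missed gain in precision. Blocking as described ensures equal group sizes only. A difference of 4 or more unilateral children between arms has roughly an 18% to 25% chance: 18% to 21% averaged over a random mix, and 24.5% if exactly 10 of 30 are unilateral. The exact figure depends on the final count; at exactly 15 of 30 only odd differences can occur, and 5 or more has a 14.3% chance. A difference of 6 or more has about a 3% to 5% chance.

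These figures assume that one-third to one-half of the children are unilateral and that allocation is from a single unstratified list. The effect on the primary result is 0.27 D for a 7 v 3 split, with D unknown.

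A reader might go further and infer that the allocation is biased or the planned test invalid. Neither follows. The consequence is a less precise estimate that is harder to interpret. Which hand is treated and which is scored is a separate matter that would remain even with perfect balance on CP type. The point is minor and cheap to settle.

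**What to change.** 1. **Analysis.** Prespecify CP type (unilateral or bilateral) as a factor in the primary T1-to-T2 between-group comparison. In the repeated-measures ANOVA the term must act on the change, that is, CP type by time; a CP-type main effect alone would leave the group-by-time test unadjusted. Cost: one degree of freedom and no extra data, since CP type is recorded at screening. Fix it before any outcome data are examined by arm.
2. **Wording.** In Outcome Measures, say that randomisation balances baseline characteristics on average and that blocking balances group size. Cost: none.
3. **Optional.** For children not yet randomised (at least 30 − 11 = 19 as of June 2026), the independent researcher could prepare separate block lists and envelope series for the two CP types. Blocks of up to 6 would hold the difference among those children to 3 at most. Against this, the scheme changes after recruitment has begun, and short separate lists are easier to predict when the treating physiotherapist is unblinded. Final sizes may also leave 15/15: two lists of blocks of 6 that each stop mid-block could leave 13/17 or worse. If the sponsor keeps the single list, items 1 and 2 are sufficient.

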**Objective:**

This study primarily aims to investigate the effects of NMES and Leap Motion–based exercise interventions on hand function in children with spastic CP and to compare the effectiveness of these 2 modalities. The secondary objective is to evaluate and compare the effects of these interventions on wrist extensor muscle activation, wrist joint range of motion, selective motor control, and hand use in daily activities.

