**Methods:**

This study is a 2-arm, parallel-group randomized controlled trial with a 1:1 allocation ratio and will include 30 children aged 6‐15 years with spastic CP and distal upper extremity involvement. All participants meeting the inclusion criteria will undergo baseline assessments at T0, where wrist range of motion will be measured using an electronic goniometer; selective motor control will be evaluated using the Selective Control of the Upper Extremity Scale (SCUES); hand function will be assessed using the Jebsen-Taylor Hand Function Test; daily hand use will be evaluated using the ABILHAND-Kids questionnaire; and wrist extensor and flexor muscle activation will be assessed using surface electromyography (sEMG). All participants will then undergo a 4-week conventional exercise program (3 sessions per week, 40 minutes per session). At the end of the 4 weeks, all baseline measurements will be repeated (T1). Subsequently, participants will be randomly assigned into 2 groups: the Leap Motion group (n=15) and the NMES group (n=15). Both groups will participate in an 8-week exercise program consisting of 3 sessions per week, 60 minutes per session (including 20 minutes of either Leap Motion–based exercise or NMES application, followed by 40 minutes of conventional exercise). At the end of this 8-week program, all assessments will be repeated (T2).

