### Interventions

This study consists of 5 sequential phases. In the first phase, eligibility of the participants will be assessed according to the predefined inclusion criteria and written informed consent will be obtained. In the second phase, baseline assessments will be conducted (T0). In the third phase, all participants will undergo a 4-week conventional exercise program before randomization, followed by midintervention assessments (T1). In the fourth phase, participants will be randomized into either the Leap Motion–based exercise group or the NMES group, and both groups will receive these interventions in addition to conventional exercise for 8 weeks. In the fifth and final phase, all outcome measures will be reassessed after completion of the intervention period, and the study will be closed out (T2).

Treatment adherence will be monitored using standardized follow-up forms, including session attendance, completed sessions, missed sessions, and adherence to the intervention protocol. All interventions in the NMES and Leap Motion–based training groups as well as the conventional exercise program will be conducted by the same pediatric physiotherapist with at least 8 years of experience. In addition, external rehabilitation programs will be discontinued after enrollment in this study.

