### Conventional Exercise Program

All participants who meet the inclusion criteria and provide informed consent will be enrolled in a 4-week conventional exercise program. The conventional exercise program will be administered 3 times per week, with each session lasting 40 minutes. The program will be structured at the beginning of the treatment period by selecting exercises from a predefined pool of neurodevelopmental treatment–based upper extremity exercises, including bilateral and unilateral upper extremity weight-bearing activities for tone regulation, passive stretching, muscle strengthening, and active ROM exercises. To improve fine motor skills, activities targeting reaching, grasping, releasing, carrying, in-hand manipulation skills, and bimanual use will also be included. The exercises will be selected and incorporated into the program based on each child’s level of impairment and clinical needs. After randomization, the selected exercises will be applied consistently across sessions for 8 weeks in addition to the group-specific interventions. While the session duration and frequency will remain standardized, exercise intensity will be adjusted by modifying the number of repetitions according to the child’s tolerance and performance.

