Weakness of prolonged wrist extensors combined with increased flexor spasticity has been associated with poorer hand function, and interventions aimed at facilitating wrist extension to modify muscle characteristics related to hand dysfunction have been suggested to improve hand function in children with CP [52]. In studies, RCTs involving LMC interventions in CP have generally assessed muscle strength using a hand dynamometer and a pinch meter to measure grip strength [22,27,45]. In RCTs involving NMES interventions, grip strength has been evaluated using a hand dynamometer [48], computerized dynamometer [53], and sphygmomanometer [46]. However, only one randomized controlled study has assessed wrist extensor muscle activation using sEMG [38]. This highlights that the use of objective, muscle-specific activation measures in CP has not been widely implemented in RCTs. The present research aims to evaluate isolated wrist extensor and flexor muscle activation using sEMG and demonstrate the effects of both interventions on the wrist extensor muscles objectively.

For clinical interpretation, changes in JTHFT scores will be considered in relation to previously reported minimal clinically important difference values in children with CP, including 54.7 seconds for the more affected hand and 20.9 seconds for the less affected hand [26]. For secondary outcomes, established minimal clinically important difference values are limited or not clearly defined in this population; therefore, the magnitude and direction of change, effect sizes, and available measurement properties will be considered when interpreting clinical relevance.

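### Three visits cannot separate each add-on's own effect from continued conventional exercise; only the NMES versus Leap Motion difference is identified

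*Protocol article*

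**What the plan says.** The schedule is clear and consistent across sections.

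- **T0 to T1.** Before randomization, "all participants will complete a 4-week standardized upper extremity–focused conventional therapy program" (Outcome Measures). The dose is given under Conventional Exercise Program: "The conventional exercise program will be administered 3 times per week, with each session lasting 40 minutes".
- **T1 to T2.** After randomization, "both groups will receive these interventions in addition to conventional exercise for 8 weeks" (Interventions). The Abstract gives the dose: "Both groups will participate in an 8-week exercise program consisting of 3 sessions per week, 60 minutes per session", made up of 20 minutes of the add-on and 40 minutes of conventional exercise.
- **Arms.** There are two, Leap Motion and NMES, allocated 1:1 (Study Design). Neither continues on conventional exercise alone.

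Outcome Measures places the run-in outside the randomized comparison and bases the main comparison on the between-group difference in T1 to T2 change. Its closing sentence then claims that the three visits provide something that "allows differentiation between the effects of conventional therapy and intervention-specific effects".

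The objective in the Abstract has two parts. The study "primarily aims to investigate the effects of NMES" and of Leap Motion exercise on hand function, and it also aims to compare the two. The Statistics section lists the group and time main effects and their interaction under the heading of primary intervention effects. Bonferroni-corrected pairwise comparisons follow if a main or interaction effect is significant.

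**The concern.** Separating an intervention-specific effect from a conventional-therapy effect requires knowing what conventional therapy alone would have produced between T1 and T2. No child provides that information. Each arm's T1 to T2 change combines the add-on with continued conventional exercise, maturation and repeat practice on a timed test.

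The T0 to T1 change cannot fill the gap. It covers half the time and half the conventional dose. It is an uncontrolled before-after change, and it includes the withdrawal of outside rehabilitation at enrollment. The exercise content may also shift, since "exercise intensity will be adjusted by modifying the number of repetitions" to each child's tolerance and performance.

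What is at stake is what the trial may conclude. If the arms do not differ, a significant time effect could be taken, on the strength of the closing sentence, as evidence that both add-ons work. The data could not support that conclusion. The limitations in the Discussion do not mention the lack of a conventional-only comparator.

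**Working it through.** The plan gives no figure to reproduce here; the question is what the design can estimate.

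**Step 1: dose in each period** (Abstract Methods, Conventional Exercise Program)

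- T0 to T1, conventional: 4 weeks × 3 sessions × 40 min = 480 min.
- T1 to T2, conventional: 8 × 3 × 40 = 960 min.
- T1 to T2, add-on: 8 × 3 × 20 = 480 min; total 8 × 3 × 60 = 1,440 min.
- Ratio of conventional dose: 960 / 480 = 2.0. Ratio of duration: 8 / 4 = 2.0.

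**Step 2: what the visit means identify**

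Let μ be the T0 mean and c1 the T0 to T1 change. Let c2 be the change from T1 to T2 that would occur without any add-on (conventional exercise, time and practice together). Let L and N be the add-on effects of Leap Motion and NMES. The expected means are:

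| | T0 | T1 | T2 |
|---|---|---|---|
| Leap Motion | μ | μ + c1 | μ + c1 + c2 + L |
| NMES | μ | μ + c1 | μ + c1 + c2 + N |

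There are four distinct means and five unknowns, so the design matrix has rank 4 for 5 parameters. Adding any constant k to both L and N and subtracting k from c2 leaves every mean unchanged. Therefore L, N and c2 are each not estimable. The difference in T1 to T2 change, (c2 + L) − (c2 + N) = L − N, is estimable.

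The time effect over T1 to T2, averaged over equal arms, is c2 + (L + N)/2. With L = N = 0 it still equals c2.

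L and N become estimable only in one of two ways: by assuming c2 = r × c1 with r known, or by adding an arm on conventional exercise alone, whose T2 mean μ + c1 + c2 supplies the fifth equation (rank 5 of 5).

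**Step 3: size of the ambiguity**

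Assume, for illustration only, a run-in gain of 10 s on the hand function test and no effect of either add-on. The protocol gives no value for r, so a range is shown.

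| r | T1 to T2 gain, both arms (s) | Apparent add-on effect after subtracting the 10 s run-in gain (s) | L − N (s) |
|---|---|---|---|
| 0 | 0 | −10 | 0 |
| 0.5 | 5 | −5 | 0 |
| 1 | 10 | 0 | 0 |
| 2 | 20 | +10 | 0 |

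The row r = 2 corresponds to gains linear in dose. The data cannot tell whether any of these patterns comes from r or from a real add-on effect. The between-arm difference is correct in every row.

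**The case against.** The strongest reply is that the protocol already bases its inference on the right contrast. Outcome Measures keeps the run-in out of the randomized comparison, names the between-arm T1 to T2 change as the main comparison, and describes randomizing after T1 as a way to compare the additional effects of the two add-ons. The only stated hypothesis, in the Introduction, is comparative. All of this stands. A reader might infer that the trial rests on before-after reasoning or that its primary comparison is flawed; the text does not support that.

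Three other strong readings should also be avoided.

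- **Within-arm efficacy tests are planned.** Statistics specifies only pairwise comparisons conditional on a significant main or interaction effect. It does not say that within-arm tests will be used to claim efficacy. The risk comes from the time effect being listed with the primary intervention effects, not from a stated rule.
- **The T1 to T2 gain will be double.** That holds only under linearity. Gains may plateau, and some of the practice effect may be used up by T1.
- **The Discussion's aim to "demonstrate the effects of both interventions on the wrist extensor muscles objectively" shows the error in the primary objective.** That sentence concerns surface EMG, a secondary outcome, so it is weak evidence about the primary objective.

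A milder defense is that T1 serves simply as a post-run-in baseline. That justifies T1, but it does not rescue the closing sentence, because conventional exercise continues after T1.

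**Conclusion.** The closing sentence of Outcome Measures claims a property that the design lacks. Three visits in two arms, both continuing conventional exercise, identify the relative effect of the two add-ons and not the effect of either one. The first clause of the primary objective, read as the effect of each intervention, therefore cannot be answered.

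The conclusion rests only on the stated schedule and number of arms. It requires no assumption about effect size or correlation, and no sample size or other figure in the protocol changes. The size of any misattribution is unknown: with no add-on effect, the T1 to T2 gain could plausibly range from none to about twice the run-in gain, depending on a dose-response that the trial does not measure. The main comparison remains valid. This is a correction to what may be claimed and should be made before results are interpreted.

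**What to change.** 1. **Outcome Measures, closing sentence:** limit it to saying that T1 provides a baseline after the run-in and that the between-arm difference in T1 to T2 change estimates the relative effect of the two add-ons on top of conventional exercise.
2. **Objective:** align the first clause with that comparison.
3. **Statistics:** state that the time main effect and any within-arm pairwise comparisons describe uncontrolled change and do not show that either add-on works. Whether p-values accompany them is a reporting choice; the labelling is what matters.
4. **Limitations:** add that, without a conventional-only arm, finding no difference between the arms would not show that either add-on is effective.

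The cost is wording only. Arms, procedures, sample size and main comparison stay as they are. According to the Results section, analysis waits until all participants have finished, so there is still time. The trial gives up only a claim it could not support.
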